#### Predictors of LBP treatment

Additional analyses will identify predictors of the dichotomous outcome of ‘chiropractic referral’ using logistic regression with PCP and patient factors serving as predictor variables. This analysis will be repeated with other PCP recommendations (e.g., opioid prescription) as outcome for model. This will provide preliminary information on whether PCP and patient characteristics that predict referral to chiropractic care also predict referrals to other guideline concordant or discordant treatments. We will use exploratory analysis (multi-level predictors of chiropractic referral) to explore which baseline characteristics predict chiropractic referral for LBP using logistic regression. We will build a general model using the ‘chiropractic referral’ outcome as the dependent variable with patient and provider characteristics as independent variables.

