### Patient population

During the fourteen-month study period, we will identify all patients aged 18 or older who have a diagnosis of LBP documented in the EHR by their PCP at a participating clinic. This will include acute or chronic LBP with or without leg pain using appropriate ICD codes (e.g., M54.5, M54.1, M54.16, M54.41, M54.42, M54.31, M54.32, M48.06, M48.07, M51.16, M51.17, M99.83, S33.5) [36]. We will exclude patients with a red flag diagnosis suggesting serious pathology may be the cause of LBP (e.g., cauda equina syndrome, cancer, spine infection or fracture). We will also exclude patients who had a primary care visit for LBP within the prior 90 days. Thus, patients with LBP may enter our study more than once if they have a new episode of LBP with 90 days between primary care visits.

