### Patient and PCP characteristics

For patients with an index visit for LBP during the study period, we will collect information from the EHR on demographic characteristics (e.g., age, gender, race/ethnicity), specific LBP diagnosis (e.g., lumbago, lumbar radiculopathy, lumbar spinal stenosis), comorbid health conditions, and prescription of an opioid or other pain medications in the prior year.

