#### Adoption of chiropractic care and other LBP treatments

Adoption of chiropractic care and other LBP treatments will be presented as the proportion of index visits each month receiving a particular PCP order type. We anticipate that adoption of chiropractic care will be our primary outcome in a future large fully powered cluster randomized trial with other PCP treatment recommendations being important secondary outcomes. The adoption of chiropractic care or other LBP treatments will be illustrated in figures showing the prevalence of orders over the study period.

In the analysis of adoption of chiropractic care, we will create a dichotomous measure “chiropractic referral” (yes/no). We will compare chiropractic referrals before the deployment of the implementation strategy and after deployment begins (i.e., pre-implementation vs. [deployment + follow-up]). The proportion of LBP patients receiving a chiropractic referral for these two time periods will be calculated. The numerator will be those with a chiropractic referral, defined as those LBP patients who received a referral, and the denominator will be all eligible LBP patients. We will use random effects logistic regression adjusting for fixed and random effects at the clinic level and a fixed effect for time of deployment of implementation strategy to estimate the change in the proportion of CHC patients with LBP who are referred to chiropractic care. While main analyses will evaluate initial referrals (i.e., those placed within 21 days of index visit), we will also explore delayed referrals in sensitivity analyses (i.e., referrals placed 22 to 89 days following index visit).

The above analyses will then be repeated to evaluate changes in other LBP treatments over the study period. We will compare the proportion of LBP patients who are referred to other nonpharmacologic treatments (e.g., PT, acupuncture), prescribed pain medications (e.g., opioids), referral to imaging (e.g., MRI), or referral to medical specialist (e.g., sports medicine, orthopedics). We will also identify interventional procedures for LBP (e.g., epidural injections, surgery) documented in the EHR during the study period.

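### The exploratory predictor models carry no implementation-phase term, so a patient or PCP factor that is unevenly spread over control and exposed visits may absorb part of the strategy's effect

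*Protocol article*

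**What the plan says.** In the Protocol article, the section Predictors of LBP treatment describes the covariates of its models twice. The first statement is "using logistic regression with PCP and patient factors serving as predictor variables". The second, for the general model, takes chiropractic referral as the "dependent variable with patient and provider characteristics as independent variables". The same approach is carried to other outcomes: "This analysis will be repeated with other PCP recommendations (e.g., opioid prescription) as outcome for model". The section calls this work additional, exploratory and preliminary. It names no analysis set and no term for phase, time or clinic.

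The visits come from the whole study. Under Patient population: "During the fourteen-month study period, we will identify all patients aged 18 or older who have a diagnosis of LBP". The section describing the characteristics of patients and PCPs sets the same window for the factors themselves: "For patients with an index visit for LBP during the study period, we will collect information from the EHR on demographic characteristics".

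The preceding section, on adoption, treats phase as the exposure: "We will compare chiropractic referrals before the deployment of the implementation strategy and after deployment begins", with the contrast given as "pre-implementation vs. [deployment + follow-up". Its model is described as "adjusting for fixed and random effects at the clinic level and a fixed effect for time of deployment of implementation strategy". The predictor section neither repeats these terms nor refers back to them.

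**The concern.** The trial is built to raise referral at deployment, so phase should be one of the strongest determinants of the outcome. A pooled model without it lets other variables stand in for it. A factor can differ between control and exposed visits in two ways:

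- **Drift within clinics.** The mix of PCPs, the diagnosis codes used or prior-year prescribing may change over the fourteen months.
- **Differences between clinics.** The staggered start gives each clinic a different share of exposed months, so a factor that is commoner in the clinic randomised first is also commoner among exposed visits, even if nothing changes over time inside any clinic.

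Either way the point estimate moves. Cluster-robust standard errors or a shorter list of predictors would not correct it. A separate report on patient and PCP predictors is planned (Discussion). Its readers could take a factor that partly tracks deployment for a characteristic that drives referral.

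**Working it through.** The article gives no sample size, effect size or expected result for these models, so there is no figure to reproduce. The check asks how far a factor with no true effect would move.

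**Schedule (Study design).** The first clinic has 4 months pre-implementation, then 2 + 8 = 10 exposed months. Each later clinic starts two months after the one before.

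| Clinic (randomised order) | Control months | Exposed months | Exposed share |
|---|---|---|---|
| First | 4 | 10 | 10/14 = 71% |
| Second | 6 | 8 | 8/14 = 57% |
| Third | 8 | 6 | 6/14 = 43% |
| All | 18 | 24 | 24/42 = 57% |

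**Assumptions.** The control referral rate is p0 = 4%; the article cites under 5% for acute LBP. The strategy odds ratio is 3. Visit volume per clinic-month is equal, and all clinics share the same p0. Exposed odds are 3 × 0.04/0.96 = 0.125, so p1 = 0.125/1.125 = 11.1%.

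**Formula, drift within clinics.** Let the factor's share be f0 in control and f1 in exposed visits. Referral among visits with the factor is

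a = (18·f0·p0 + 24·f1·p1) / (18·f0 + 24·f1),

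and among visits without it, b is the same expression with 1 − f0 and 1 − f1. The spurious odds ratio is [a/(1 − a)] / [b/(1 − b)].

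**Worked case, share 20% to 30%.**

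- a = (18 × 0.2 × 0.04 + 24 × 0.3 × 0.1111) / (3.6 + 7.2) = 0.944/10.8 = 8.74%
- b = (18 × 0.8 × 0.04 + 24 × 0.7 × 0.1111) / (14.4 + 16.8) = 2.443/31.2 = 7.83%
- odds ratio = (0.0874/0.9126) / (0.0783/0.9217) = 1.13

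**Between-clinic route, shares 80%, 50%, 20%, no drift.** Clinic referral rates over the fourteen months are (4p0 + 10p1)/14 = 9.08%, (6p0 + 8p1)/14 = 8.06% and (8p0 + 6p1)/14 = 7.05%. Then a = (0.8 × 9.08 + 0.5 × 8.06 + 0.2 × 7.05)/1.5 = 8.47%, b = (0.2 × 9.08 + 0.5 × 8.06 + 0.8 × 7.05)/1.5 = 7.66%, and the odds ratio is 1.12.

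**Results for a factor with no true effect.** Logistic models were fitted to the expected cell counts under these assumptions:

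| Distribution of the factor | Factor only | Factor + clinic | Factor + phase |
|---|---|---|---|
| 20% to 23% | 1.04 | 1.04 | 1.00 |
| 20% to 25% | 1.07 | 1.06 | 1.00 |
| 20% to 30% | 1.13 | 1.12 | 1.00 |
| 20% to 50% (extreme) | 1.34 | 1.32 | 1.00 |
| 80/50/20 by clinic, no drift | 1.12 | 1.00 | 1.00 |

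**Range.** With a strategy odds ratio of 2 the factor-only results are 1.03, 1.04, 1.08, 1.22 and 1.08. With 5 they are 1.06, 1.09, 1.18, 1.48 and 1.16. With 1 they are all 1.00.

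**How much is absorbed.** At a strategy odds ratio of 3, the 10-point shift moves the factor's log odds ratio by log(1.128)/log(3) = 11% of the strategy's. The 30-point shift moves it by log(1.342)/log(3) = 27%.

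**The case against.** The strongest reply is that the section is a sketch. It speaks of building a general model and of multi-level predictors, never says outright that all fourteen months are pooled, and may leave adjustment terms to a fuller plan. The team plainly knows about the deployment term, since its adoption model has one. This stands in part: pooling is inferred from the absence of any restriction. But the article does more than stay silent. It states the covariates twice, as patient and PCP characteristics only, right after a section that lists the deployment and clinic terms.

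Several other objections stand:

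- Nothing in the article shows PCP turnover, coding change or demographic drift at these clinics. The shifts above are assumptions, and a 20% to 50% change at deployment is extreme.
- The between-clinic route is equally an omitted-clinic problem, since clinic effects alone remove it. Clinic order is randomised, so its direction is a matter of chance.
- With three clinics and referral under 5%, clinic fixed effects would take up much of the variation in PCP factors, and phase-stratified tables could be sparse. A heavier remedy is therefore debatable.

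A reader might infer that any unevenly spread factor takes on the whole of the strategy's effect, or that false findings will be common. The documents do not support either. Only a fraction of the effect is absorbed, none of it if the strategy does not work, and a false-positive rate would need visit volumes that the article does not give.

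**Conclusion.** The concern holds as a minor point about exploratory models. As written, they leave out the variable that the trial manipulates. If the strategy changes referral and a factor is unevenly spread over control and exposed visits, its odds ratio may partly reflect the strategy. With a 4% control rate and a strategy odds ratio of 3, the distortion is small for modest imbalance: 1.04 to 1.13 for shifts of 3 to 10 points from 20%, and 1.12 for a marked imbalance between clinics. It reaches 1.34 only in the extreme case. It vanishes if the strategy has no effect or if the factor's share is the same in control and exposed visits.

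These sizes rest on equal visit volumes and a common baseline rate across clinics. If baseline rates differ by clinic, a phase term alone does not remove confounding by clinic. For opioid prescription and the other orders, no size can be given, because the article does not say how far the strategy would change them.

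It would be too strong to conclude that the predictor work is invalid or that the trial's results are at risk. The feasibility outcomes and the adoption comparison do not depend on these models, and the article declares the pilot underpowered for adoption outcomes.

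**What to change.** Add one sentence to Predictors of LBP treatment, for example: *All predictor models, for chiropractic referral and for other PCP recommendations, will include implementation phase (pre-implementation versus deployment and follow-up combined) as a covariate.* This uses the two-level exposure already defined for the adoption analysis.

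The cost is one parameter per model and no new data, since phase is already needed for the adoption comparison. Clinic adjustment is better kept as a sensitivity analysis, because with three clinics it absorbs much of the between-clinic variation in PCP factors. Associations within control and within exposed visits can be shown descriptively where referral counts allow. That would also separate who was referred before the strategy from who is referred under it.

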### Adoption of chiropractic care and other treatments

Adoption of chiropractic care will be measured through PCP referrals to chiropractic care. We will extract this information from the EHR based on orders placed following an index visit with a PCP for LBP. The rate of adoption for a given month will be the proportion of index visits where an order for chiropractic care is placed within 21 days. This period of time is based on a recent study showing that most patients receive at least one order within 21 days of an initial visit to their PCP for acute LBP and that orders after 21 days are uncommon [12]. This study also found that < 5% of participants with acute LBP received an order to chiropractic care within 21 days [12]. Additionally, we will identify other recommendations documented in the EHR by PCPs within 21 days of the index visit. These will include: (1) other evidence-based nonpharmacologic treatments (e.g., acupuncture, massage, physical therapy); (2) prescribed pain medications (e.g., NSAIDs, opioids); (3) referral to imaging (plain x-rays, MRI), or referral to specialists (e.g., sports medicine, orthopedics) who may offer interventional procedures (e.g., epidural injections, surgery).

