PCPs will be invited to complete an online survey to gather additional information on sociodemographic characteristics (e.g., age, sex, race and ethnicity), pain experiences, attitudes/beliefs regarding chiropractic care, and additional constructs that may predict adoption of chiropractic care. Prior personal experiences of pain and pain treatment may influence PCP management decisions for their patients with LBP. Thus, PCPs will be asked about current or previous personal experiences of musculoskeletal pain including the location(s) and duration of pain. The 3-item PEG Pain Screening Tool will be used to assess their pain on average, how much the pain has interfered with their enjoyment of life, and how much the pain has interfered with their general activity [51]. Each question is scored from 0 to 10 with higher scales indicating worse pain. PCPs will be asked if they have received chiropractic care (yes/no) and, if yes, whether their experience was positive, neutral, or negative. Additionally, we will ask PCPs to self-report patterns of referring to DCs using questions from the National Ambulatory Medical Care Survey [52] including “Have you referred to a chiropractor in the past 12 months?” with participants responding “yes/no” and “How often have you referred your patients to chiropractic care in the past 12 months?” with participants responding “weekly, monthly, quarterly, a few times per year, never”. Attitudes and beliefs towards chiropractic care for LBP will also be captured by adapting questions from previous studies of chiropractic care in primary care [53] and chiropractic experiences among medical students [54]. To understand the acceptability, appropriateness, and feasibility of routine chiropractic care use for LBP among PCPs, we will adapt questionnaires developed by *Weiner et al.*: The Acceptability of Intervention (AIM), Intervention Appropriateness Measure (IAM), and Feasibility of Intervention Measure [55]. Each questionnaire includes four items and a corresponding 5-point Likert scale, allowing responses to range from 1 (strongly disagree) to 5 (strongly agree) for each item. Higher scores indicate greater acceptability, appropriateness, and feasibility [55]. 

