Our plan for dissemination of findings includes several reports. First, the main outcomes and analyses described in this protocol will be published in a timely manner following trial completion. Second, we anticipate publishing at least one additional manuscript that summarizes themes of qualitative interviews on barriers and facilitators of chiropractic care for LBP. Third, we will develop a report on patient and PCP characteristics that predict adoption of chiropractic care in primary care clinics. We posit that the size of the local DC workforce and the geographic location of chiropractic clinics may also be associated with adoption of chiropractic care in primary care clinics. Thus, a fourth planned manuscript will use geospatial analysis to explore access to chiropractic care in neighborhoods of Boston that are near participating CHCs. In addition to our scholarly articles, we will work with the participating CHCs and our advisory board (described below) to explore the best method to widely communicate lessons learned from this work [63]. Study data will be made available on formal request to the principal investigator and following completion of a data use agreement.

After completing the implementation phase at all three sites, we will form an advisory board to provide feedback on developed implementation strategies and to provide additional guidance on how to scale or transfer strategies in additional CHCs or other healthcare settings. Additional strategies may also be needed in future implementation efforts. We will seek guidance from the advisory board on any barriers that emerge during our ongoing site visits and stakeholder interviews. The use of advisory committees has been part of the approach to implementing chiropractic care in the Veterans Health Administration [64]. The advisory board will be made up of local and national experts including leaders from other CHCs who may serve as sites for future trials. The results from a future large trial could inform policy makers on the need to sustain this approach to help reduce PCP workload, reduce overall spine care costs (reductions in use of imaging or procedures), and increase treatment safety (reduce opioid use).

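### The predictor models test PCP characteristics with plain logistic regression and name no term for visits clustered within PCP, so standard errors for PCP-level predictors would be too small

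*Protocol article*

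**What the plan says.** All places are in the protocol article.

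- **Predictors of LBP treatment.** Predictors of referral are to be found "using logistic regression with PCP and patient factors serving as predictor variables". The same analysis is repeated for other PCP orders, such as an opioid prescription. A general model is then built "with patient and provider characteristics as independent variables". The section describes its aim this way: "We will use exploratory analysis (multi-level predictors of chiropractic referral) to explore which baseline characteristics predict chiropractic referral". It names no random effect, cluster-robust variance, clinic term or implementation-phase term.
- **Adoption of chiropractic care and other LBP treatments (Data analysis).** The before-and-after comparison of the same referral outcome uses random effects logistic regression, with clinic effects and a fixed effect for time of deployment.
- **Patient and PCP characteristics.** The PCP survey covers demographics, the PCP's own pain, attitudes to chiropractic care and "additional constructs that may predict adoption of chiropractic care". All of these are attributes of the PCP, not of the visit.
- **Patient population.** A patient may enter again with a new episode if 90 days separate the primary care visits.
- **Discussion, dissemination plan.** A separate output is promised: "we will develop a report on patient and PCP characteristics that predict adoption of chiropractic care in primary care clinics".

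**The concern.** Referral is recorded once per index visit, but a PCP characteristic takes one value per PCP. For such a predictor, the independent information comes from the number of PCPs rather than the number of visits. Ordinary logistic regression counts every visit as independent. If PCPs differ in their readiness to refer beyond what the model explains, the fitted standard errors are too small and the p-values too low.

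The protocol's own reasoning makes such differences likely. It collects PCP attitudes and personal pain history because these may shape how a PCP manages LBP.

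The PCP factors named in the planned report could then be chance differences between a limited number of clinicians at three clinics. Clinic and implementation phase matter as well. The strategy is meant to change referral, and PCPs are nested in clinics that switch at different times.

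**Working it through.** The protocol states no sample size, number of PCPs, visits per PCP, intra-PCP correlation or parameter count, so it has no figure of its own to reproduce. The inputs below are assumptions unless marked as the protocol's.

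**1. Design effect for a PCP-level predictor**

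- Assumed visits per PCP, m = 40.
- Assumed intra-PCP correlation of referral, given the other predictors, ρ = 0.05 to 0.10.

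The variance is understated by a factor of 1 + (m − 1)ρρₓ, where ρₓ is the within-PCP correlation of the predictor. For a PCP characteristic ρₓ = 1.

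| ρ | Design effect | Standard error understated by |
|---|---|---|
| 0.05 | 1 + 39 × 0.05 = 2.95 | √2.95 = 1.72 |
| 0.10 | 1 + 39 × 0.10 = 4.90 | √4.90 = 2.21 |

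For a patient characteristic that does not itself cluster by PCP, ρₓ is near 0 and the factor is near 1.

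**2. What this does to a nominal 5% test**

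The false-positive rate is 2 × [1 − Φ(1.96/k)], where k is the understatement of the standard error.

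- k = 1.72: 1.96/1.72 = 1.14, giving about 25%.
- k = 2.21: 1.96/2.21 = 0.89, giving about 38%.

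**3. Check by simulation**

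Plain logistic regression was fitted to data with three PCP-level and three patient-level predictors, none with any true effect. The set-up was 70 visits per PCP, a PCP random effect with SD 0.8 on the logit scale and a referral rate near 5%, with 200 replicates.

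| PCPs | PCP-level predictors significant at 5% | Patient-level predictors significant at 5% |
|---|---|---|
| 30 | 28.5% | 5.3% |
| 60 | 26.7% | 5.0% |

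The two routes agree. An SD of 0.8 at a 5% rate corresponds approximately to ρ = 0.8² × 0.05 × 0.95 = 0.030. With 70 visits this gives 1 + 69 × 0.030 = 3.1, a standard error ratio of about 1.76 and an expected false-positive rate of about 27%. Doubling the number of PCPs did not remove the problem. The simulation had no repeat episodes, so it says nothing about that further source of dependence.

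**4. Events per parameter**

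Three clinics over 14 months (protocol) give 42 clinic-months. Events per parameter = visits per clinic-month × 42 × referral rate ÷ parameters. With an assumed 20 parameters and a 5% rate:

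| Visits per clinic-month | Referrals | Events per parameter |
|---|---|---|
| 20 | 42 | 2.1 |
| 50 | 105 | 5.2 |
| 100 | 210 | 10.5 |
| 200 | 420 | 21 |

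At a 1% rate the same volumes give 0.4 to 4.2. The schedule gives 4 + 6 + 8 = 18 clinic-months before deployment and 42 − 18 = 24 after it starts. If the rate were 5% before and 10% after, 100 visits per clinic-month would give 100 × (18 × 0.05 + 24 × 0.10) = 330 referrals, or 16.5 per parameter.

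A separate null simulation with independent visits and 20 predictors gave per-test false-positive rates of 4.5%, 4.5%, 4.9% and 5.4% at 1.6, 3.2, 5.3 and 10.5 events per parameter.

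**The case against.** **The analysis is only exploratory, and details belong in the SAP.** The protocol does call the work exploratory and its output preliminary, and this limits the weight of the point. But the label does not correct a standard error, and a dedicated report is planned. Nor is this just an unstated detail. The text names the model, and the neighbouring section names a different one, with random effects, for the same outcome. The phrase about multi-level predictors describes where the predictors sit, not a multilevel model. The unseen SAP may supply the missing term, and if it does the point is closed.

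**The size rests on assumed inputs.** This is correct. With few visits per PCP or little variation between PCPs, the understatement shrinks towards none.

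**A stronger reading is tempting.** A reader might infer that every listed characteristic goes into one model of a very rare outcome, so that there are far too few referrals per parameter and spurious predictors follow. The document does not support this:

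- It does not say that all characteristics are entered, and it gives no parameter count or selection rule.
- It gives no visit count. LBP patients per month is itself a feasibility outcome.
- The low rate belongs to a cited study: "This study also found that < 5% of participants with acute LBP received an order to chiropractic care within 21 days". This trial also includes chronic LBP and visits after a strategy meant to raise referrals.
- Events per parameter fall on both sides of 10 over plausible inputs, and low values alone did not raise false positives per test.

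Penalisation, a ten-events rule and the choice of candidates, including whether to keep self-reported past referral, are preferences or matters for the SAP. The document also does not say that this model will steer tailoring of the strategy. Tailoring is informed by interviews.

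**Conclusion.** The concern holds for clustering. As written, the predictor models would give standard errors that are too small for PCP-level characteristics. The understatement is about 1.7 to 2.2 times under the assumed 40 visits per PCP and correlation of 0.05 to 0.10. Null PCP-level predictors were significant in about 27% to 29% of tests in a simulation with its own assumed clustering. The direction is firm wherever PCPs differ in referral beyond the modelled factors, but the size is not known from the document. Patient-level predictors are largely unaffected by PCP clustering.

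Sparse events remain a conditional risk that can be judged only when the referral count is known. The point is minor. It concerns an exploratory analysis and leaves the trial's feasibility outcomes and the adoption comparison untouched.

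**What to change.** State in the section on predictors of LBP treatment that the models for chiropractic referral and for the other orders will:

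1. include a random intercept for PCP, or report intervals from a bootstrap that resamples whole PCPs. Resampling PCPs also keeps together repeat episodes of a patient seen by the same PCP;
2. include clinic and implementation phase as fixed covariates. Three clinics are too few to estimate a clinic variance well;
3. report the number of PCPs alongside the number of visits, since that number governs precision for PCP factors.

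The number of candidate predictors can be set once the referral count is known and before the models are fitted.

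The cost is a few lines of analysis wording and standard software. Intervals for PCP factors will be wider and fewer such factors will be identified, which reflects how much information the PCPs at three clinics can give.
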